#### Data management

The ethical principles of the data handling and integrity were discussed with and approved by the Institutional Review Board (IRB). During the study a dedicated study nurse, supervised by the principal investigator, is responsible for completion and storage of the case record forms (CRFs). Hard copies of the CRFs are kept in a separate and secured filing cabinet within the department/study site. Data entry into the password protected study database is performed by the study nurse as well.

#### Study integrity

The study has been designed and will be conducted and reported in accordance with SPIRIT STATEMENT [67] and was registered (DRKS00009758) in “The German Clinical Trials Register” [68].

#### Sample size

We intend to recruit 200 participants. The sample size calculation was based on the study report by Mozaffari-Khosravi et al. [69] as the most comparable RCT. They applied the BDI-II as primary outcome measure in a population of adult depressed patients and observed a difference of four BDI-II score points between treatment arm (single dose vitamin D; 150 I.E.) and control group. Since the study was conducted in adults, we further looked for RCTs in adolescents with major depressive disorders, irrespective of vitamin D as the treatment item [70, 71], revealing a standard deviation of nine BDI-II score points as input for the sample size calculation, which yielded finally a sample size of 81 participants (two-sided t-test; alpha = 0.05; powered at 80% to detect a true difference). Attrition [72] was assumed to be 20%, demanding a recruitment of 100 participants per intervention arm.

#### Data analyses and statistical hypothesis

Analysis of the data will be conducted by a researcher blinded to the treatment condition. All statistical analyses will be performed after database-lock with “R” (www.r-project.org) at the Institute for Medical Biometry und Epidemiology (IMBE), Philipps-University Marburg, Marburg, Germany.

The main hypothesis of this study is, that treatment of depressive symptoms results in significantly lower improvement of BDI-II scores in the group of patients with vitamin D deficiency (placebo group) than in the supplementation group (verum group). The statistical hypothesis to be tested for the mean BDI-II score in the verum arm versus the placebo arm after 28 days of supplementation:

Null hypothesis: H_0_: BDI-II_verum_ = BDI-II_placebo_.

Alternative Hypothesis: H_1_: BDI-II_verum_ unequal BDI-II_placebo_.

A covariance analysis (ANCOVA) will be performed to contrast the outcome of the primary endpoint BDI-II in both intervention arms (two-sided level of significance; alpha = 0.05) in the Intention-To-Treat (ITT) population. The following co-variables will be considered: BDI-II at admission, 25(OH)D level at admission, age, and sex. Missing values will be considered via Last-Observation-Carried-Forward (LOCF) data, as far as available. Several sensitivity analyses will be conducted to prove for robustness, encompassing a per protocol analysis.

The secondary endpoint 25(OH)D and PTH levels will also be analyzed in the ITT population via an ANCOVA with the co-variables: 25(OH)D level at admission, age, and sex.

Further sensitivity analysis will be performed e.g. non-parametric analysis where patients with missing data will be set to lowest or highest ranks and repeated measure models will be applied. to hopefully confirm the results.

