## Methods

### Study design

The study is set up as a 28 days (based on the mean length of hospitalization of juveniles with depression), parallel group, double-blind, randomized, placebo-controlled trial to investigate the effect of an untreated vitamin D deficiency (placebo arm) on depressive symptoms in child and adolescent psychiatric patients.

We are currently enrolling 200 participants at one study site, the Department of Child and Adolescent Psychiatry, University Hospital Essen, University of Duisburg-Essen, Essen, Germany. In total, recruitment, intervention, and database lock are anticipated to be finalized within a two years period after First-Patient-First-Visit (FPFV).

Patients with a vitamin D deficiency, who meet the inclusion criteria (see below) and consented to the study will be randomized to receive either 2640 I.E. vitamin D q.d. based on recommendations for treatment of vitamin D deficiency in patients with chronic diseases (REF) or placebo on top of treatment-as-usual (TAU). Participants will be assessed psychometrically prior to study start and after 28 days with the self-rated Beck-Depression-Index –II [52] (BDI-II; selected instrument for inclusion criteria and primary endpoint) and additional psychological instruments (Table 1).

**Table 1 Tab1:** Scheduled measurements

Investigated item	Psychometric and sociometric questionaires/instruments	Executed /completed by	Time point(s)	Reference
Depression	BDI-II	Patient	Baseline, and end of study	[83]
Depression	DISYPS-II DES SBB	Patient	Baseline and end of study	[84]
Depression	DISYPS-II DES FBB	Parents	Baseline and end of study	[84]
Intelligence and mental development status	IQ,HAWIK, CFT, Son-R	Patient	Baseline	[85]
Structured Interview for clinical diagnosis	KIDDIE-SADS-PL	Clinical interviewer	Baseline	[66, 86]
Impulsivity	BIS	Patient	Baseline and end of study	[87]
Problem behaviors	CBCL	Parents	Baseline	[88, 89]
Problem behaviors	YSR	Patient	Baseline	[88]
Socioeconomic status	SES (KiGGS)	Parents	Baseline	[90]
Vitamin D status related questionnaire	SUN EXP QUEST	Patient	Baseline	[91, 92]
Habitual food and nutrient intake	FFQ	Patient	Baseline	[54]
Physical Activity	IPAQ	Patient	Baseline	[62]

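### Primary LOCF rule with a single scheduled post-baseline BDI-II: drop-outs without an exit assessment are analysed as unchanged, which dilutes or biases the treatment estimate

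*Protocol article*

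**What the plan says.** The section Data analyses and statistical hypothesis makes the primary analysis a two-sided ANCOVA of the BDI-II in the ITT population. The covariates are admission BDI-II, admission 25(OH)D, age and sex. The missing-data rule follows directly: "Missing values will be considered via Last-Observation-Carried-Forward (LOCF) data, as far as available". A per-protocol analysis, a rank analysis that places patients with missing data at the lowest or highest ranks, and repeated-measures models are listed as sensitivity analyses.

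Under Study design, participants are "assessed psychometrically prior to study start and after 28 days", and Table 1 gives baseline and end of study as the only BDI-II time points. Data collection and outcome measures mentions the BDI-II at the first clinic visit and again on the second day. Both precede randomization, which takes place on days three to five after admission.

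The same section applies the end-of-study procedure at premature study end, if this is possible and the participant accepts. Patients discharged early keep their pill dispensers, are telephoned weekly and are asked back at day 28. No BDI-II is mentioned for the calls.

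Under Sample size: "Attrition [72] was assumed to be 20%, demanding a recruitment of 100 participants per intervention arm".

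**The concern.** LOCF needs a last observation that is a credible stand-in for the missing one. Here a drop-out without an exit assessment has nothing after randomization, so the value carried forward is the admission score, which had to exceed 13 for entry. Both arms receive guideline treatment, and the main hypothesis is worded as a smaller improvement on placebo than on verum, so improvement is expected in both arms. Carrying the admission score forward sets that improvement to zero. An exit score is better, but it still treats a patient part-way through treatment as if at day 28.

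The primary estimate is at stake. Equal drop-out mixes a block of zero changes into both arms and dilutes the difference. Unequal drop-out places more zero changes in one arm, so part of the improvement under usual treatment appears as a treatment effect, or hides one.

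The sample size also does not match the rule. It treats the 20% as lost from the analysis, whereas LOCF keeps them in.

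**Working it through.** **The plan's own figure.** Inputs from Sample size: "observed a difference of four BDI-II score points", "revealing a standard deviation of nine BDI-II score points", and "two-sided t-test; alpha = 0.05; powered at 80% to detect a true difference".
- Normal approximation: n = 2 × (1.960 + 0.842)² × 9² / 4² ≈ 79.5, so 80 per arm. The exact two-sample t-test gives 80.44, so 81 per arm, as stated ("yielded finally a sample size of 81 participants").
- Attrition: 80 / 0.8 = 100, or 81 / 0.8 = 101.25, so 102. The stated 100 is close enough. In the other direction, 100 × 0.8 = 80 patients with a day-28 value, so the plan counts drop-outs as absent.

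**Assumptions not in the documents.** Placebo improvement 8 points; baseline/day-28 correlation 0.5; drop-out unrelated to outcome; an exit score, where given, lies halfway through the patient's change. SD 9 and 100 per arm come from the plan.

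**Expected LOCF estimate, by arithmetic.** With a true difference of 4, improvement is 8 on placebo and 12 on verum.

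| Drop-out placebo / verum | Exit scores | Expected LOCF difference |
|---|---|---|
| 20% / 20% | none | 0.80 × 12 − 0.80 × 8 = 3.2 |
| 20% / 20% | half | 3.2 + 0.20 × 0.5 × 0.5 × 4 = 3.4 |
| 15% / 25% | none | 0.75 × 12 − 0.85 × 8 = 2.2 |
| 25% / 15% | none | 0.85 × 12 − 0.75 × 8 = 4.2 |

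With no true effect and 15% / 25% drop-out, the bias is (0.25 − 0.15) × 8 = 0.8 points against verum. If half give an exit score, it is 0.10 × 0.75 × 8 = 0.6, because the average drop-out then loses 1 − 0.5 × 0.5 = 0.75 of the improvement.

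**Simulated ANCOVA** (adjusted for baseline BDI-II; Monte Carlo error about 1 percentage point or less).

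| Scenario | LOCF, no exit scores | LOCF, half give one | Observed day-28 values |
|---|---|---|---|
| Power, true difference 4, 20% / 20% | 77% | about 86% | 89% to 90% |
| Type I error, 20% / 20% | 5% | 5% | 5% |
| Type I error, 15% / 25% | about 11% to 12% | about 8% to 9% | 5% |

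The half-uptake entry for type I error at 20% / 20% was run at improvements of 5, 10 and 15 rather than 8, and was 5% each time.

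**Range over the assumptions.** With improvement 5 to 15 points, correlation 0 to 0.5 and 20% drop-out per arm, LOCF power is 53% to 83% without exit scores and 65% to 88% with half. Observed values give 79% to 90%. Type I error at 15% / 25% (correlation 0.5, improvement 5 to 15) is 8% to 21% without exit scores and 6% to 15% with half.

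**The case against.** The strongest reply is that the plan does not leave drop-outs with a baseline score only. It offers an exit BDI-II and follows early-discharged patients to day 28, so early discharge is not in itself drop-out. That stands. A reader might infer that all or most drop-outs are analysed as unchanged, but the documents give no uptake for the exit assessment and do not support this. Uptake therefore has to be shown as a range; at half uptake the loss is smaller but still there.

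A reader might also infer that LOCF always shrinks the effect or generally inflates type I error. Neither holds. With more drop-out on placebo the estimate can exceed the truth, and with equal drop-out type I error stays at 5%. At 18% against 22% it is about 6%. The plan gives one attrition figure and identical-looking pills, so nothing in it predicts a large imbalance.

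The alternative is not immune either. If improvers are the ones who leave (15% against 25%, with an assumed probit slope of 0.8), ANCOVA on observed values has a bias of 0.64 points and a type I error of 8.6%. LOCF is worse, at 1.0 points and 17%, but missing-at-random is an assumption too.

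The LOCF sentence could be read as carrying only post-baseline values forward. Its wording does not settle this. Patients without an exit score would then have no value in an analysis labelled ITT, so the sentence needs replacing on either reading.

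The extreme-rank analysis does stress the missing-data assumption, but it leaves the primary estimate as it is.

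Two further inferences should not be drawn. Applying the diluted difference to the t-test of the sample size section does not give the power of the trial, because the planned analysis is a baseline-adjusted ANCOVA. Extending LOCF to 25(OH)D goes beyond the text: the rule stands in the primary-endpoint paragraph, and the secondary paragraph states no missing-data rule.

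**Conclusion.** The point holds in this conditional form. The protocol fixes as primary a rule that, for any drop-out without an exit assessment, uses a pre-treatment score as the day-28 outcome in patients who are expected to improve.

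Under the stated assumptions and the plan's own 20% attrition, the cost with equal drop-out is 0.6 to 0.8 of the 4 points and roughly 4 to 13 percentage points of power, depending on exit-score uptake, with type I error intact. With drop-out of 15% against 25% and no true effect, the bias is 0.6 to 0.8 points and type I error about 8% to 12%.

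The correlation, the improvement, the uptake and the imbalance are all assumed. The direction of the mechanism does not depend on their exact values, but its size does.

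**What to change.** Before database lock, replace the LOCF sentence:

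- **Primary:** the same ANCOVA with the same covariates under missing-at-random. Use multiple imputation by arm from admission BDI-II, 25(OH)D, age and sex, with any exit BDI-II as an auxiliary value rather than as the day-28 outcome. An equivalent likelihood-based model would also serve. With one scheduled post-baseline visit, a repeated-measures model adds little over ANCOVA on observed values unless it uses the exit scores.
- **Sensitivity:** move LOCF here, and state whether admission scores may be carried forward. Next to the planned extreme-rank analysis, add a delta-adjusted analysis that varies the departure from missing-at-random separately by arm, because missing-at-random is itself biased if drop-out depends on the unobserved outcome.

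The cost is a change of wording and a little more programming, with no extra patients or visits. The downside is that the primary result then relies on missing-at-random, which the delta-adjusted analysis is there to test.

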### Study aims

Within this two-armed, double-blind, randomized controlled trial we aim to test the hypothesis that moderate to severely depressed children and adolescents (BDI-II sum score at admission > 13) with a vitamin D deficiency (25(OH)-D3 level < 30 nmol/l [equivalent to < 12 pg/ml]) who will be treated as usual, but will not be supplemented with vitamin D (*placebo* arm) for a period of at maximum 28 days, will end-up with a significantly higher BDI-II sum score, than those immediately supplemented with 2640 I.U. vitamin D3 q.d. (*verum* arm). The assessment of the vitamin D status is not part of current routine diagnostic in clinical psychiatric departments or psychiatric offices. This study is to the best of our knowledge the first randomized controlled trial (RCT) investigating the effect of watchful waiting with regard to vitamin D supplementation in children and adolescent inpatients with an elevated depression score. The primary outcome parameter is the BDI-II sum score. Secondary outcome parameters encompass the 25(OH)-D levels from baseline to study end as well as impulsiveness and depressive symptoms assessed with parent- and self-rating instruments.

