#### Exclusion criteria

Exclusion criteria include: a concurrent diagnosis of a severe somatic disease, (ascertained by the assessment of the medical history and medical examination at inpatient admission), renal disease, hypocalcemia and/or a blood plasma parathyroid hormone (PTH) level > 130 ng/ml, mentaI retardation (IQ < 70). Patients, who present with vitamin D deficiency and established hypocalcemia or PTH level > 130 ng/ml in the recruitment phase, will be excluded, referred to pediatric endocrinology for further assessment and treatment, including initiation of immediate treatment with vitamin D3.

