#### Screening assessment

Potentially eligible patients, who present to the University Duisburg-Essen Department of Child and Adolescent Psychiatry and who will be scheduled for hospital admission, will be informed about the ongoing study by a physician. If patients and parents are interested in an enrolment into the study and sign the written consent, patients will be asked to complete the BDI-II questionnaire [52] on the day of admission as the “primary endpoint intstrument” as well as the other psychological instruments as specified in Table 1. On the day of admission serum/plasma levels of 25(OH)D, calcium and parathyroid hormone will be determined in addition to the the clinical routine lab work.

Medical and psychiatric history will be obtained by the admitting physician to ensure eligibility. In this context the auxiologic parameters body height, weight, BMI and Tanner status [53] will be assessed and recorded as well as basic clinical parameters (e.g. blood pressure).

Potential participants and their parents will be asked to complete several psychometric and sociometric questionnaires, and for assessment of dietary intake a food frequency questionnaire (FFQ) [54], which was specifically designed to assess the food and nutrient intake with a particular focus on fatty acids of school-aged children in Germany and a questionnaire regarding several questions to explore factors influencing the vitamin D status as e.g. time spent outdoors and sun-shield use (see Table 1). In addition, the status of omega-3 long-chain fatty acids (n-3 LC-PUFA) in erythrocytes [55, 56], will be determined at baseline [57, 58]. First studies have shown reduced n-3 LC-PUFA levels in depressed adolescents in contrast to healthy matched controls [56].

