#### Data collection and outcome measures

Blood samples and a spot urine sample will be collected in the Department of Child and Adolescent Psychiatry as part of the clinical routine at admission. After written consent is obtained, the aliquots will be transferred at 4° within an hour after collection according to documented and approved standard operation procedures (SOPs) to the central laboratory of the University Hospital Essen. 25(OH)vitamin-D3, PTH and serum calcium levels will be measured and reported on the same day to a pediatric endocrinologist for approval. In addition electrolytes (including calcium), the differential blood count (DBC), thyroid-stimulating hormone level, inflammatory markers, liver and renal parameters, and alkaline phosphatase will be analyzed and reported.

Data for eligible participants will be transferred to the study nurse for further processing and inclusion into the CRFs. Remaining aliquots of blood samples and urine will be stored in at − 80 degree until further analyses. Planned assays are related to neutrophines, metabolites and hormones involved in metabolic signaling cascades. In case of consent from study participants and parents, DNA/RNA will be retrieved and stored for potential follow-up investigations of genetic variants and expression profiles of vitamin D metabolism related genes and gene products, respectively.

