At the end of the study (at day 28 of the intervention) participants will complete the BDI-II/ DISYPS-II -DES [52, 59] and additional instruments as depicted in Table 1. A blood sample for the determination of 25(OH)D levels will be obtained. The same procedure will be applied – if possible and accepted by the participant – in case of premature study end (drop-out for any reason). In case of discharge from hospital before 28 days, participants will be asked to continue supplementation with the handed-out pill dispensers in the scheduled manner. These outpatient participants will be followed-up weekly by phone and asked to show up for the end-of-study examination at day 28 after study start.

A technical plausibility and completeness check of the data will be performed after data entry by a non-scientific assistant at the Institute for Medical Biometry und Epidemiology, Philipps-University Marburg (IMBE).

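### The PTH ANCOVA borrows the covariates chosen for 25(OH)D and so omits PTH at admission; the sections on PTH as a day-28 endpoint also need reconciling

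*Protocol article*

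**What the plan says.** All references are to the protocol article.

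- **Data analyses and statistical hypothesis, secondary model.** One sentence covers 25(OH)D and PTH together as a secondary endpoint and ends: "PTH levels will also be analyzed in the ITT population via an ANCOVA with the co-variables: 25(OH)D level at admission, age, and sex".
- **Same section, primary model.** For BDI-II the list is: "The following co-variables will be considered: BDI-II at admission, 25(OH)D level at admission, age, and sex". It includes the outcome's own baseline.
- **Screening assessment.** "On the day of admission serum/plasma levels of 25(OH)D, calcium and parathyroid hormone will be determined".
- **Data collection and outcome measures, admission.** "25(OH)vitamin-D3, PTH and serum calcium levels will be measured and reported on the same day to a pediatric endocrinologist for approval".
- **Exclusion criteria.** Admission PTH decides eligibility, because patients are excluded for "hypocalcemia and/or a blood plasma parathyroid hormone (PTH) level > 130 ng/ml".
- **Data collection and outcome measures, day 28.** "A blood sample for the determination of 25(OH)D levels will be obtained". PTH is not mentioned there.
- **Study aims.** "Secondary outcome parameters encompass the 25(OH)-D levels from baseline to study end as well as impulsiveness and depressive symptoms assessed with parent- and self-rating instruments". PTH is not mentioned there either.

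**The concern.** An ANCOVA of a follow-up measurement gains most of its precision from the baseline value of the same measurement. The plan follows that principle for BDI-II and for 25(OH)D but not for PTH, where the baseline of a different analyte stands in. No reason is given, and the likeliest explanation is that the 25(OH)D list was carried over unchanged. What is at stake is a wider confidence interval and lower power for the PTH comparison, when the missing covariate should already be on file for every randomised patient.

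The second part is a mismatch between sections. The analysis section plans to compare PTH between arms, which presupposes a follow-up value. The section that describes the day-28 blood sample gives only 25(OH)D as its purpose, and the aims do not count PTH among the secondary outcomes. A site working from the text could reasonably omit the assay.

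**Working it through.** **1. The plan's own figures.** The article states no effect size, standard deviation, correlation or power for PTH, so there is no PTH figure to reproduce. Its sample size concerns BDI-II: a difference of 4, SD 9, two-sided alpha 0.05 and 80% power. The exact two-sample t-test gives 80.44, rounded up to the stated 81 per arm. That calculation does not bear on PTH. From the Sample size section I use only 100 per arm and 20% attrition, that is 100 × (1 − 0.20) = 80 completers per arm.

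**2. Is the missing covariate available?** Yes. PTH is determined on the day of admission, reported the same day, and used as an exclusion criterion. If the plan is followed, every randomised patient has a value.

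**3. Precision lost.** Let ρ be the within-arm correlation between admission and day-28 PTH, and r the correlation between admission 25(OH)D and admission PTH. Neither is in the article, so both are assumptions: ρ = 0.3, 0.5 or 0.7, and r from 0 to −0.3. I also assume that admission 25(OH)D predicts day-28 PTH only through admission PTH. Age and sex are left out because they are in both models. With day-28 PTH in SD units:

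- residual variance, plan's model = 1 − (rρ)²
- residual variance with admission PTH added = 1 − ρ²
- ratio = [1 − (rρ)²] / (1 − ρ²)

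Results for r = 0 and r = −0.3:

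- ρ = 0.3: 1/0.91 = 1.10; 0.9919/0.91 = 1.09
- ρ = 0.5: 1/0.75 = 1.33; 0.9775/0.75 = 1.30
- ρ = 0.7: 1/0.51 = 1.96; 0.9559/0.51 = 1.87

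**4. What the ratio means.** Confidence-interval width scales with the square root of the ratio. For an effect that the model with admission PTH would detect with 80% power, the power of the plan's model is Φ[(1.960 + 0.842)/√ratio − 1.960]. With 80 per arm, the smallest difference detectable with 80% power is 2.802 × √(2/80 × residual variance), in SD units.

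| ρ (assumed) | Variance ratio | Interval wider by | Power of plan's model | Detectable difference, plan's model | Detectable difference, with admission PTH |
|---|---|---|---|---|---|
| 0.3 | 1.09-1.10 | 4-5% | about 76% | 0.44 SD | 0.42 SD |
| 0.5 | 1.30-1.33 | 14-15% | 68-69% | 0.44 SD | 0.38 SD |
| 0.7 | 1.87-1.96 | 37-40% | 52-53% | 0.43-0.44 SD | 0.32 SD |

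**5. The sections side by side.** Analysis section: PTH is analysed with the secondary endpoint. Aims: the secondary outcomes are named without PTH. Day-28 procedures: blood is drawn, with 25(OH)D as the stated purpose. Table 1 lists questionnaires and interviews, not laboratory tests, so it does not settle the matter. The Fig. 1 caption defines the abbreviation PTH, but the figure is not shown and may refer to screening only.

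**The case against.** **Shorthand in a condensed article.** One covariate list shared by two analytes may be compression, and the full protocol or analysis plan may give each analyte its own baseline. That is possible and lowers confidence that the error exists in the full plan. It does not make the published wording right: the list is explicit and does not fit PTH.

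**Other models.** The analysis section also announces repeated-measures models among its sensitivity analyses. If applied to PTH, these could use the admission value. Their scope is not stated, and a sensitivity analysis would not repair the main PTH model.

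**Size.** The loss rests entirely on assumed correlations. At 0.3 it is about 10% of variance, and excluding patients with high PTH may lower the correlation by narrowing its range. This stands, and it is why the result is given as a range.

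**Three stronger readings that a reader might infer are not supported:**

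- *That the PTH analysis cannot be run.* The day-28 sentence names 25(OH)D but does not exclude PTH, the flow chart is not visible, and the planned analysis itself implies a follow-up value. The text supports only that no visible section schedules the assay.
- *That the PTH comparison is biased.* Randomisation protects it. A chance imbalance in admission PTH is part of the sampling error that the model's standard error already reflects; what is lost is precision.
- *That BDI-II at admission must also enter the laboratory models because it is a randomisation stratum.* Nothing in the article suggests that it predicts 25(OH)D or PTH, so no benefit is shown. The 25(OH)D stratification variable is already in these models.

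The aims may also not be meant as an exhaustive list, so that mismatch alone is editorial.

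**Conclusion.** The point holds as a minor one. As published, the PTH ANCOVA leaves out the endpoint's own baseline, which is collected anyway, while the primary model and the 25(OH)D model each include theirs. The cost is precision, not validity: residual variance of about 1.1, 1.3 or 1.9-2.0 times what is attainable, for assumed admission-to-day-28 correlations of 0.3, 0.5 or 0.7 and the mediation assumption stated above. Separately, the aims, the day-28 procedures and the analysis section do not agree on whether PTH is a day-28 endpoint. Neither matter touches the primary BDI-II analysis.

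**What to change.** 1. In the data analyses section, separate the two laboratory models. Keep 25(OH)D at admission, age and sex for 25(OH)D. For PTH, add PTH at admission; the other three covariates can stay.
2. Reconcile the three sections. Either name PTH as an assay on the day-28 blood sample and list it among the secondary outcomes in the aims, or remove PTH from the secondary analysis.

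**Cost.** The covariate change is wording only and uses data already collected. It should be made before database lock, since the analyses are planned for after it. If PTH is kept and is not already being assayed at day 28, the cost is one more assay on blood that is drawn anyway. Enrolment was under way when the article was written, and it describes storage of leftover aliquots in connection with the admission samples without stating this for day 28. Day-28 PTH may therefore not be recoverable for patients who have already finished, so the question should be settled promptly.
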